### Aim

The aim of this study is to measure the impact of the new RTSA road safety bus stickers in PSVs encouraging passengers to speak out against reckless driving on RTCs involving minibuses. The primary outcome of interest will be the difference in road traffic crashes between buses with and without the new RTSA road safety bus stickers.

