### Sample size and selection

For a conservative measure of effect, and thus a more conservative and larger sample size, we propose a difference-in-difference primary analysis examining data from 7 months before compared to the 7 months after the implementation of the intervention (and not disaggregated into monthly measures). Based on budget constraints and logistics, we estimated the minimal person time for minibuses assuming we would like to see a minimal effect of 0.01 absolute difference in the *change* in the accident rate per 1000 minibuses over the 14-month period (7-month pre vs. 7-month post). This change is similar to that of the Kenya study. Table 1 presents the inputs used for this equation, assuming the accident rate reported within the Kenya study among the controls would be generalizable to Zambia [20]. To account for potential spillover due to the fact that passengers will transfer between buses (though we assume drivers to remain within the same buses), we assumed that the control arm would have slight improvement in the accident rate over the 14-months observed. Additionally, the equation assumes an alpha of 0.05 and power (beta) of 80%. The equation used is as follows [22]:$$ N\  person- years\ in\ each\  arm={\left({Z}_{\frac{\alpha }{2}}+{Z}_{\beta}\right)}^2\Big[\left({\lambda}_0+{\lambda}_1\right)/{\left({\lambda}_0-{\lambda}_1\right)}^2 $$

**Table 1 Tab1:** Sample size calculation parameters

Z_a/2_	Type I error	1.96
Z_B_	Type II error	0.84
*λ* _0_	Estimated change in the accident rate per 1000 minibuses over the 14-month period in the control arm	−0.01
	Absolute difference	.01
*λ* _1_	Estimated change in the accident rate per 1000 minibuses over the 14-month period in the intervention arm	−0.02
y	Number of person years in each arm	116
	Number of cars assuming cars followed for 1.16 years or 14 months	954
	Number of vehicles to follow with 10% buffer per arm	1060

The sample size calculation formula in Table 1 used is adopted from Hayes & Mouton (2009). A buffer of 10% was included to allow for buses that may drop out of the study during recruitment for any reason

For the big buses, there is a finite sample of buses and we intend to enroll all big buses from within the sampled areas.

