### Study outcomes (Table 2)

ᅟ

**Table 2 Tab2:** Study Outcomes

No.	Study Comparison	Variable	Indicator	Source
1. Primary Outcome Indicator				
1	Difference between intervention and control buses	Change in traffic crash rate per 1000 buses over a 14-month period	Whether the bus experienced a road traffic crash as reported from motor vehicle insurance claims among those buses during 7-month period of study or 7-months prior to study	Data on motor vehicle insurance claims
2. Secondary Outcome Indicators				
2	Difference between intervention and control buses	Change in the traffic crash rate per 1000 buses overtime for a 14-month period (monthly analysis)	Whether the bus experienced a road traffic crash as reported from motor vehicle insurance claims for each month for the 7-month period of study or 7-months prior to study (repeated measures or monthly analysis)	Data on motor vehicle insurance claims
3	Difference between intervention and control buses	Change in crashes resulting in fatalities per 1000 buses over a 14-month period	Total number of fatalities from road traffic crashes during the period of the study as compared to the 7 months prior to the study	Data on motor vehicle insurance claims
4	Pre vs. Post (overall and not separated per arm)	Mean number of road traffic crashes	Total number of road traffic crashes during the period of the study as compared to the 7 months prior to the study	RTSA data and Zambia road traffic police reports;

Lists one primary outcome of interest and three secondary outcomes of interest. The primary source of information will be data from motor vehicle insurance claims while road traffic police reports will be used for only one secondary outcome

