### Data analysis

At endline, full analysis will be performed using data from the full 14-month period. To assure balance between the study arms, we will compare characteristics between our two arms including insurance company provider and accident rates in the past year. Additionally, utilizing the insurance claims data, we will compare the insurance claim rate per 1000 vehicles in the 7 month period before the intervention.

For the primary outcome of the study in which will examine the change in the road traffic accident rate over the 14-month period for the intervention arm compared to the change in the road traffic accident rate over the 14-month period for the control arm, we will use a difference-in-difference analysis. To this end, we will run a difference-in-difference analysis that will be comparing the intervention and control groups using regression analysis of the following format, and adjusting the SE to account repeated measures (i.e. cluster) from the bus:$$ {\mathrm{Y}}_{\mathrm{rate}}={\upbeta}_0+{\upbeta}_{\mathrm{Sticker}}{\mathrm{X}}_1+{\upbeta}_{\mathrm{Post}}{\mathrm{X}}_2+{\upbeta}_{\mathrm{Sticker}\mathrm{Post}}{\mathrm{X}}_3+\mathrm{e} $$

For the primary outcome regression, Y is the occurrence of a road traffic crash (indicator 1, 0); X_1_ is the indicator for whether or not the bus was in the intervention arm or control arm (i.e. 0, 1); X_2_ is the indicator for the time period with a value of one indicating the seven-month post intervention period; X_3_ being the interaction indicator between the presence of the new RTSA road safety sticker and the post intervention period (difference-in-difference impact estimate). Additionally in this regression above, the β_Sticker_ estimate will provide the relative difference in the accident rate between intervention and control arm during the pre-intervention period; β_Post_ will be provide the relative change in the accident rate in the control group from pre- to post- intervention period; and, β_StickerPost_ will be the relative difference between the control and intervention group in the change in the outcome from pre to post intervention (i.e. our main estimate of effect). We will appropriately adjust for baseline imbalance between the two arms including insurance provider. To assure outcomes are more meaningful, the rates and thus betas for outcome 1 and 2 will be transformed to report per 1000 minibuses. This regression will then be replicated for the remaining study outcomes.

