We will run the difference-in-difference analysis assuming intent-to-treat (ITT), in that all of those who received the assigned new RTSA road safety bus sticker (even vs. odd) will have placed the new RTSA road safety bus sticker accordingly. Though it is expected that the monitoring of RTSA will not provide perfect fidelity to the specific arms, the ITT analysis will provide a conservative estimate of effect.

Due to the nature of the study, drivers and participants cannot be blinded, however, it will be helpful to examine the effect of the new RTSA road safety bus stickers overtime to determine if Hawthorne effects, the process by which a subject of a study changes their behavior due to the knowledge that they are being surveyed and measured, reduces overtime (outcome 2). To this end the regression presented above will become a controlled interrupted time series (ITS) where each minibus will have an observation for each month for the 7-months before the intervention and 7-months after the sticker placement – a form of repeated measures analysis.

In sensitivity analysis, we will examine the difference between the study periods in our primary outcome (seven-month accident rate) controlling for baseline differences.

For outcomes with a comparison over time but not between the two study arms (outcome 4), we will run a general t-test comparison between the RTC rates before and after the intervention as well as a regression analysis controlling for any differences at baseline.

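### As worded, the sensitivity analysis of the primary outcome compares the periods before and after the stickers, not the arms, so it cannot check the between-arm result

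*Protocol article*

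**What the plan says.** The protocol article defines the primary question as a comparison of arms in three places.

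- Aim: "The primary outcome of interest will be the difference in road traffic crashes between buses with and without the new RTSA road safety bus stickers".
- Study outcomes (Table 2), comparison column for outcome 1: "Difference between intervention and control buses".
- Data analysis: the main estimate is the sticker-by-post coefficient, which "will be the relative difference between the control and intervention group in the change in the outcome from pre to post intervention".

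The same section explains the period coefficient of that model. It is the "relative change in the accident rate in the control group from pre- to post- intervention period", so it is not a measure of the sticker.

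Later in Data analysis comes the one sentence labelled as a sensitivity analysis: "In sensitivity analysis, we will examine the difference between the study periods in our primary outcome (seven-month accident rate) controlling for baseline differences". It names the periods and the baseline adjustment, but no arm term. The next sentence turns to a different group: "For outcomes with a comparison over time but not between the two study arms (outcome 4". Table 2 declares that outcome as before versus after, on agency and police data.

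**The concern.** A sensitivity analysis should put the same question under different assumptions. The primary question here is whether the change over time differs between arms. The sensitivity sentence, read as it stands, asks whether the claims-based crash outcome changed over time.

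Season, enforcement or claim-filing habits can move that outcome in both arms alike, and adjusting for baseline differences between buses does not remove a shift they all share. Season is a live example. If the 14 months run consecutively, the pre months are 1 to 7 and the post months 8 to 14. Only months 13 and 14 repeat a calendar month of the pre period (1 and 2), so season and period largely coincide. The randomised concurrent controls exist to remove this kind of shift, and a pure period contrast sets them aside.

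The risk is a misleading companion result: apparent support when only time has moved, or apparent doubt when a time change offsets a sticker effect. The Discussion says the evaluation is meant to inform national scale-up.

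**Working it through.** The article gives no figure for the sensitivity analysis, so there is none to reproduce. The check has two parts.

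**What each contrast estimates.** Let *t* be a change over time common to both arms and *d* the additional change in sticker buses. With equal arms:

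- Difference-in-difference: (*t* + *d*) − *t* = *d*.
- Post-period difference between arms, with equal baselines: *d*.
- Period contrast pooled over arms: [*t* + (*t* + *d*)]/2 = *t* + *d*/2.

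The period contrast therefore holds half of the sticker effect plus all of the common change, and it cannot separate them.

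**How often the period contrast rejects when *d* = 0.** Inputs:

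- Buses: 954 per arm (Table 1 and Randomization), so 2 × 954 = 1908 per period. I take this number as stated; 954/0.9 = 1060 reproduces the enrolment target.
- Baseline: the Discussion gives 0.026 per 6 months. It is printed per 1000 minibuses; I assume it is per bus. Scaled to 7 months: 0.026 × 7/6 = 0.0303. The unscaled 0.026 is shown as the other end of the range.
- Test: two-sided 5%, with crashes taken as independent between periods.
- Size of *t*: -0.01, the figure Table 1 gives for the control-arm change, used here only as an illustrative size; and smaller values.

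Formula: SE = √[p₀(1−p₀)/1908 + p₁(1−p₁)/1908], z = |t|/SE, rejection ≈ Φ(z − 1.96) + Φ(−z − 1.96).

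*t* = -0.01, baseline 0.0303: SE = √(0.0303×0.9697/1908 + 0.0203×0.9797/1908) = 0.0051; z = 1.97; rejection about 50%.

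*t* = -0.005, baseline 0.0303: SE = √(0.0303×0.9697/1908 + 0.0253×0.9747/1908) = 0.0053; z = 0.94; rejection about 16%.

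*t* = -0.005, baseline 0.026: SE = √(0.026×0.974/1908 + 0.021×0.979/1908) = 0.0049; z = 1.02; rejection about 17%.

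Simulation at 954 per arm, baseline 0.0303 (20,000 trials):

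| Common change | Period contrast | Difference-in-difference | Post-period arm contrast |
|---|---|---|---|
| 0 | 5% | 5% | 5% |
| -0.0025 | 7% | 5% | 5% |
| -0.005 | 15% | 5% | 5% |
| -0.01 | 50% | 5% | 5% |
| +0.005 | 14% | 5% | 5% |
| +0.01 | 39% | 5% | 5% |

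With 1060 per arm, the period contrast rejects in 54% at -0.01 and 17% at -0.005. With baseline 0.026 and 954 per arm, a 4,000-trial simulation gave 59% and 19%. The formula and a larger simulation of 200,000 trials give 58% and 17%, so 19% is a little high.

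**The opposite case.** With *d* = -0.01 and *t* = +0.005, the pooled contrast is 0.005 − 0.005 = 0. It rejects in 5% of trials, the difference-in-difference in 15% and the post-period arm contrast in 25%.

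**The case against.** The strongest reply is that the wording is a slip and the authors meant arms. Data analysis uses baseline adjustment for imbalance between arms, and such adjustment has little purpose in a within-bus before-after contrast. Only outcome 4 is set apart as not compared between arms. A seven-month rate suggests a single period's outcome. This is plausible and may well be right, so nobody should infer that the authors deliberately chose a before-after test. But the sentence still names the wrong contrast. If it instead means an adjusted difference-in-difference, it repeats the primary analysis, which already adjusts for baseline imbalance. It needs correcting on each reading.

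Other limits also stand.

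- A reader might infer that the trial has no arm-based check. The documents do not support that. This is a journal article, and further analyses may sit in a fuller plan. The monthly analysis of outcome 2 extends the regression that carries the arm terms. The point rests on what the sentence says, not on what is absent.
- A reader might infer that the period contrast has nothing to do with the sticker. It holds half of the effect; the trouble is confounding.
- The -0.01 in Table 1 is not offered as a calendar trend. Sample size and selection ties it to spillover: "we assumed that the control arm would have slight improvement in the accident rate over the 14-months observed". A fall of 0.01 from 0.0303 is also a one-third drop in crashes. The 50% is an illustration, not a forecast.
- In the offsetting case the correct primary analysis rejects in only 15% of trials, so most of the missed effect there is low power.
- The article does not say that the arms would be pooled, nor that any conclusion depends on the sensitivity analysis.

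**Conclusion.** The point holds in a limited form. As worded, the sensitivity analysis of the claims-based primary outcome is a before-after contrast, while the Aim, Table 2 and the primary model all define a between-arm question. Taken literally it confounds the sticker with time and cannot check the primary result. The difference-in-difference analysis itself is untouched.

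The size depends on three assumptions: 0.026 is a per-bus risk, the arms are pooled, and periods are independent. On those, with 954 per arm and no sticker effect, false rejection is about 50% for a common change of -0.01 and about 15 to 17% for -0.005. At -0.0025 it is only 7%, so it would be wrong to conclude that any time trend makes the analysis significant. Read literally per 1000, the baseline implies 0.0303/1000 × 1908 = 0.06 expected crashes per period, and no test would be informative. The logical mismatch does not depend on these figures.

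**What to change.** In Data analysis, replace the phrase naming the study periods in the sensitivity sentence with: *the difference between the study arms in the post-intervention seven-month crash outcome, controlling for the bus's pre-intervention crash indicator and insurance provider*. This targets the same arm effect as the primary model but handles baseline differently, so agreement or disagreement means something. If a before-after change in the claims outcome is still wanted, label it descriptive and keep it apart from the sensitivity analysis.

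The cost is one sentence of wording. The pre-intervention crash indicator is already needed for the difference-in-difference, and insurance provider is already a planned adjustment variable. No extra buses or data collection are required.

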## Discussion

Given the potential infrequency of overall RTCs (0.026 per 1000 minibuses per 6 months as reported in Kenya) and the relatively short length of the study, it is possible we will not find an impact at 7 months. There is a risk that our effect may be conservatively estimated both due to the ITT analysis but also due to potential spillover effects as passengers may go between the arms of the study; however, we feel confident there may still be a potential impact of the new RTSA road safety sticker. This is because the Kenya study similarly randomized sticker placement within the same city, thus allowing for spillover, and was able to see an impact of the sticker program. Additionally, though in the sample size calculation, we accounted for a potential improvement in the accident rate over the 14-months examined in the control group, and estimate we still anticipate some spillover thus resulting in conservative effect estimation.

Though every PSV operator is mandated by law to have valid insurance cover, the use of insurance claims data for our outcome could lead to some measurement error as not everyone files insurance claims when involved in a crash. This may be primarily prevalent in those with third party insurance who may be involved in a crash with unclaimed physical objects such as trees, walk ways, barricades etc. However, RTCs involving injuries or deaths to passengers are highly likely to be reported to insurance companies.

The outcomes, analysis, and recommendations of this evaluation are expected to inform the national scale-up of the new RTSA road safety bus stickers in PSVs by RTSA. Specifically, the results will help RTSA to understand whether the toll-free bus sticker has an impact and whether the new RTSA road safety bus stickers can improve on road safety outcomes. If only limited changes are observed, then RTSA and other national road safety stakeholders will collaborate to understand the reasons and propose further adjustments.

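### The baseline rate and target effect are labelled per 1000 minibuses, a unit that cannot be reconciled with the planned sample size; the unit needs verifying and Table 1 recomputing

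*Protocol article*

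**What the plan says.** The Discussion of the protocol article judges feasibility from a crash rate of "0.026 per 1000 minibuses per 6 months as reported in Kenya".

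Under Sample size and selection, the smallest effect of interest is an absolute difference of 0.01 between arms in the change in accident rate, also per 1000 minibuses, comparing 7 months before with 7 months after. Table 1 lists -0.01 as the "Estimated change in the accident rate per 1000 minibuses over the 14-month period in the control arm" and -0.02 as the "Estimated change in the accident rate per 1000 minibuses over the 14-month period in the intervention arm". The text presents Table 1 as the inputs to a formula that returns person-years per arm. No division by 1000 and no conversion to an annual rate is shown. The table then prints 116 for "Number of person years in each arm", 954 for "Number of cars assuming cars followed for 1.16 years or 14 months", and 1060 per arm with the buffer.

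Under Data analysis, the primary outcome is coded 0 or 1 for each bus, and "the rates and thus betas for outcome 1 and 2 will be transformed to report per 1000 minibuses".

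**The concern.** A person-years formula needs events per vehicle-year. If 0.01 and 0.02 are per 1000 minibuses, they must be divided by 1000 first, and the result is then far beyond any feasible trial. If they are per bus, the label is wrong by a factor of 1000 wherever it appears.

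The time base is also unsettled. The Kenya rate is per 6 months, the changes compare two 7-month periods within 14 months, and the formula works in years.

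These figures serve to judge whether the trial can succeed and whether its result is large enough to matter for national scale-up. If the target is really 0.01 per bus, the analysis will report it as 10 per 1000, while the plan states the smallest effect of interest as 0.01 per 1000.

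**Working it through.** **Inputs.** Z values 1.96 and 0.84, changes of -0.01 and -0.02, difference 0.01, follow-up 1.16 years and 954 buses per arm (Table 1); 2110 minibuses (Abstract); 0.026 per 6 months (Discussion).

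**1. The plan's own figure.** The formula is N = (1.96 + 0.84)² × (λ0 + λ1) / (λ0 − λ1)², with (2.80)² = 7.84. The signed table values give 7.84 × (−0.03) / 0.0001 = −2,352, so absolute values are used below.

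- Per bus, taken as annual rates: 7.84 × 0.03 / 0.0001 = 2,352 person-years per arm; 2,352 / 1.16 = about 2,028 buses.
- As labelled (0.00001 and 0.00002 per bus): 7.84 × 0.00003 / 0.0000000001 = 2,352,000 person-years per arm; divided by 1.16, about 2.03 million buses.

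Neither gives 116 person-years or 954 buses. Those two printed figures also disagree with each other: 116 / 1.16 = 100 buses, whereas 954 × 1.16 = 1,107 person-years. Only the buffer reproduces: 954 / 0.9 = 1060.

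**2. A bound that does not depend on which rates were entered.** For non-negative rates the sum is at least the difference, so N is at least 7.84 / difference.

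- Difference of 0.01 per 1000: at least 7.84 / 0.00001 = 784,000 person-years per arm.
- Difference of 0.01 per bus: at least 7.84 / 0.01 = 784 person-years per arm.

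The planned 1,107 person-years lies above the second bound and about 700 times below the first (784,000 / 1,107 = 708).

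**3. Expected minibus crashes over 14 months, both arms.**

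- As labelled: 2110 × 0.026 / 1000 × 14/6 = 0.128. The Poisson probability of no crash at all is exp(−0.128) = 0.88.
- Per bus: 2110 × 0.026 × 14/6 = 128, or about 64 in each 7-month period.

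Using 2 × 1060 = 2120 minibuses changes these only to 0.129 and 129. Adding the 300 big buses at the same rate gives 0.146 as labelled.

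**4. Reporting scale, if the figures are per bus.** Target: 0.01 × 1000 = 10 per 1000. Baseline: 0.026 × 1000 = 26 per 1000 per 6 months; 26 × 7/6 = 30 per 1000 per 7 months, assuming a constant rate.

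**5. Time base, per-bus reading.** Multiplying both rates by a factor divides N by that factor. If 0.01 and 0.02 refer to 7 months, N = 2,352 × 7/12 = 1,372 person-years per arm. If they refer to 14 months, N = 2,352 × 14/12 = 2,744. Neither equals 116 or 1,107.

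**6. Power by the same formula at 1,107 person-years per arm.** Power = Φ(difference / √(sum / 1,107) − 1.96). Per bus, as annual rates: 0.01 / √(0.03 / 1,107) = 1.92, so power is Φ(−0.04), about 48%. As labelled, power is about 3%.

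**The case against.** The strongest reply is that this is a wording slip. The analysis already codes crashes per bus and converts to per 1000 for reporting, and the label may simply have been carried back into the design section. On that view about 128 crashes are expected, and nothing changes in allocation, data collection or the model. Part of this stands: per bus is the more plausible reading, and the figure of 0.13 crashes shows that the label fails rather than forecasting the trial.

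Three further parts of the reply also stand.

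- A reader might infer that the calculation was carried out with per-bus values, or requires them. The article does not show the substitution, and per-bus values do not return the printed result, so this remains an inference from order of magnitude.
- The 0.026 is not a row in Table 1. The sample-size text says only that the Kenya control rate was assumed to apply in Zambia, so no factor-1000 error in the calculation itself is shown for the baseline.
- The mismatch between target and reported estimates is conditional. Taken literally, both are per 1000 and share a scale. They part only if the target is really per bus.

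The reply fails where it treats the matter as cosmetic. The unit is attached to the target effect and to the inputs of the primary sample-size calculation, and no pair of non-negative rates in that unit comes near the planned size.

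**Conclusion.** The point holds in this form: the printed unit for the baseline, target difference and Table 1 inputs is incompatible with the design that relies on them. As labelled, the minibus trial expects about 0.13 crashes in 14 months and needs 2.35 million person-years per arm (at least 784,000), against about 1,107 planned. This rests on the printed formula with absolute values, a constant crash rate and the Abstract's 2110 minibuses.

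Per bus is the probable reading, with about 128 crashes and a target of 10 per 1000. It cannot be confirmed from the article, since the Kenya source is not shown.

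Two stronger conclusions are tempting and unsupported. One is that the trial will see almost no crashes; that follows only if the label is literally right. The other is that multiplying by 1000 repairs the plan; Table 1 still fails to reproduce after that. Because the figures define the primary target and the feasibility of the trial, this must be corrected.

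**What to change.** 1. Check the unit and time base of the Kenya rate in its source.
2. State the baseline, target difference, both Table 1 changes and the reported estimates in one unit and one time base. If the source is per bus, that means about 26 per 1000 minibuses per 6 months (about 30 per 1000 per 7 months at a constant rate) and a target of 10 per 1000.
3. Convert the rates to the annual base that the formula needs, recompute Table 1 so that person-years and buses agree, and show the substitution.
4. Since enrolment is bound by budget and logistics, restate the power or the detectable difference at the planned size.
5. If the rate really is per 1000, say plainly that the trial cannot detect the target effect.

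The cost is a source check, a recalculation, and edits to the sample-size text, Table 1 and the Discussion. Outcome data and the regression model need not change. The recalculated size may show that the planned enrolment falls short of 80% power, and the article should then say so.
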